**Data Collection Plan and Data Management**

The Data Coordination Centre (DCC) will be the Applied Health Research Centre (AHRC), an academic research organization based at St Michael's Hospital. AHRC will use software called Medidata RAVE ([www.mdsol.com](http://www.mdsol.com/)) to create the web-based electronic CRF (eCRF). All study data will be securely stored on local servers at St Michael’s Hospital throughout the duration of the study and for up to 10 years after the study is complete. All study subjects will be identified in the database by a unique study ID number. Linkages between the patient name/contact information and the study ID will be retained at the local site and not shared with the study DCC or outside the institution. At the end of the study (after all analyses are complete) the DCC will transfer all study datasets over to the study PI. Data will only be accessible by authorized study site personnel and authorized central DCC personnel. Authorized personnel receive a username and password which is unique, and database access is controlled by the DCC in collaboration with the Principal Investigator.

Three members of this research team ([name]) are Toronto site principal investigators of the At Home / Chez Soi Research Demonstration Project on Homelessness and Mental Health, a large longitudinal national program evaluation funded by the Mental Health Commission of Canada. This proposed study will utilize data collection instruments and knowledge gained from the At Home / Chez Soi study to help engage and follow frequent users of the ED. Survey interviews will be completed by research assistants (RA). The RAs, supported by a Research Coordinator (RC), will be responsible for recruiting study participants, collecting data from CATCH-ED participant clinical records to ascertain clinical diagnoses and frequency of contact with CATCH ED clinicians and administering participant survey interviews at entry point into the program and at 3, 6, 9 and 12 months following enrolment. RAs will be updating the tracking information at all participant interviews and at monthly intervals through telephone follow up with each participant. A brief summary of client measures is provided below.

*Socio-demographic variables*: Research staff will collect the following information: basic demographic information, residential status, income support status.

*Health Status*: Specific health status measures will include the SF-12, the EQ-5D, the Colorado Symptom Index, the Quality of Life Index (QoLi-20) and the alcohol and drug module of the Addiction Severity Index.

*SF- 12:* This 12-item self-report measure of generic health status is a shorter version of the SF-36 Health Survey designed to reproduce the Physical Component Summary (PCS) and Mental Component Summary (MCS) scores. It has an administration time of 2 minutes. There are 2 questions concerning physical functioning, 2 questions on role limitations because of physical health problems, 1 question on bodily pain, 1 question on general health perceptions, 1 question on vitality, 1 question on social functioning, 2 questions on role limitation because of emotional problems, and 2 questions on general mental health (psychological distress and psychological well-being). It has excellent psychometric properties. (Ware et al, 1996).

*EQ-5D:* EQ-5D is a self-administered standardized measure of health status developed by the EuroQoL Group in order to provide a simple, generic measure of health for clinical and economic appraisal. It provides a simple descriptive profile and single index value for health status. The EQ-5D descriptive system has 5 dimensions: mobility, self-care, usual activities, pain/discomfort and anxiety/depression. Each dimension has 3 levels: no problems, some problems and severe problems. The visual analog scale records the respondent’s self-rated health on a vertical, visual analogue scale where endpoints are labeled “best imaginable health state” and “worst imaginable health state”. This information can be used as a quantitative measure of health outcome as judged by the individual respondents (The EuroQuol Group, 1990; Brooks, 1996).

*Quality of Life Index (QoLI-20):* The original scale was designed to assess the quality of life of people with severe and persistent mental illness. It is a structured self-report interview, conducted by a trained non-clinical interviewer, and elicits participants’ ratings of their quality of life. There are 7 subjective scales (living situation, everyday activities, family, social relationships, finances, safety, and satisfaction with life in general) and 4 objective scales (everyday activities, enough money, family contacts, and contacts with friends). The 20-item version was developed by Uttaro et al. (1999) using item-response theory and it has retained excellent psychometric properties.

*Colorado Symptom Index (CSI):* The CSI was designed specifically for individuals with mental health problems. It is a 14-item instrument which assesses the presence and frequency of symptoms of mental illness experienced within the past month. Responses are provided using a 5-point Likert scale with answer choices ranging from 0 (not at all) to 4 (at least every day). A higher score indicates a higher level of symptoms. The Colorado Symptom Index is a widely used tool in research as a self-report measure of psychiatric symptomatology. The CSI has been reported to have excellent internal consistency (.92) and test-retest reliability (.71). Evidence of the CSI’s validity is strong as CSI scores have been proven to distinguish between individuals with and without mental health service needs and were significantly correlated with functioning(Boothroyd and Chen, 2008).

*ASI:* The alcohol and drug module of the Addiction Severity Index (ASI), the most widely used instrument in the field, will be utilized. The ASI is a structured interview instrument that yields information about the severity of lifetime and recent (previous 30 days) drug and alcohol use (McLellan et al, 1980). Five indices will be used to measure substance abuse-the number of days that alcohol or substances were abused in the past month, the amount of money spent on alcohol or drugs in the past month, and the participants’ rating of the need for alcohol or drug use treatment. The ASI has good inter-rater and test-retest reliability and good concurrent and discriminant validity. It has been used extensively with the homeless population (Hwang et al, 2005).

*Participant Service Use:* Service use events will be tracked using both self-reported and administrative data. We will establish the number of hospitalizations, days in hospital and emergency department visits during the year prior to program enrolment as well as the 12 month follow-up period. We will also collect data on non-acute service use, such as mental health, substance use, and primary care visits, using service use forms adapted from the At Home / Chez Soi project on homelessness and mental health.

*Service satisfaction – SSS10:* This scale is a shorter version of the SSS-30 (Greenfield & Attkisson, 2004) which was extensively tested in Alberta and in a few services in British Columbia (Adair et al, 2005). Participants will be asked whether they had received any assistance with an array of different care needs. The three needs categories will include: coordination of services; family and social networks and community linkages; and life skills training, support and practical needs assistance.

*Working Alliance Inventory-Participant (WAI-PAR):* This 12-item self-report measure (modified from the original 36 item version) is designed to assess the working-alliance construct based on the theory that a working alliance common to all therapeutic relationships grows out of client-therapist agreement on therapy goals, agreement on therapy tasks, and development of a strong relational bond between client and therapist (Busseri et al, 2003). There are 4 items (chosen from the longer scale using factor analysis) in each of three subscales: task, goal and bond. Items are rated on 7-point scales (1=never, 7=always). Ratings yield task, goal and bond subscale scores as well as an average score based on all items. The scale has good psychometric properties, with mean reliability estimates ranging from .79 to .97, with a modal estimate of .92 (Horvath & Greenberge, 1989; Hanson et al, 2002).

*Administrative Data Linkage*

Data linkage will be conducted at the Institute for Clinical Evaluative Sciences (ICES) where population based health information is available, at the patient level, for all Ontarians using formal health services. Subjects will be linked deterministically using their Ontario Health Card Number (encrypted at ICES to preserve anonymity). Health administrative data will be used to identify individuals’ use of hospital and physician services in a 12-month observation window preceding and following their enrolment to the CATCH-ED program. Health service use will be examined by the National Ambulatory Reporting System (NACRS), the Discharge Abstract Database (DAD), the Ontario Mental Health Reporting System (OMHRS) and the Ontario Health Insurance plan (OHIP) for ED visits, outpatient clinics and inpatient hospitalizations.

*Other Administrative Data*

Provincial databases, including the Ontario Drug Profile Viewer and the Office of the Registrar General, will be consulted in the case where participants are lost to follow up at 12 months in order to ensure that health service utilization is not affected by death or relocation to another province. Informed consent to consult these databases will be collected from participants at study entry.

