**Methods - Outcome Evaluation**

The study design is a randomized controlled trial in which multiple longitudinal outcome measures will be collected on both the intervention and control groups to assess client characteristics and selected outcomes of interest.

Frequent users will be recruited to the study over a 9-month period and followed for 12 months. Program participants will complete survey interviews at baseline, 6 and 12 months to assess health status, mental health, substance use, self reported acute care service use, service satisfaction and their working alliance with their primary clinician. Self-reported acute care use will be complemented by administrative data linkage to examine acute care service use 12 months prior and 12 months following referral to the intervention. Participants will also complete survey interviews at 3 and 9 months to assess their service use and to confirm their contact information and any time spent outside the Province during the previous three-month period.

*Sample Size Calculation*

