**Analysis Plan**

We will calculate descriptive statistics (mean, standard deviation, quartiles) and construct graphs (histograms, scatter plots, box-plots) to characterize the clients at baseline with respect to socio-demographic factors, housing status, health status, and health service use. Baseline group comparisons will be conducted using chi-square test or Fisher’s exact test (for categorical variables), t-test or Wilcoxon rank-sum test (for continuous variables). We will construct plots to describe longitudinal changes in primary and secondary outcomes over time. All analyses will use an intent-to-treat perspective and will be compared with a per-protocol analysis. The primary outcome evaluates the proportional change in rate of emergency department visits (ED visits) between pre-intervention and 6-month time intervals post-intervention; some secondary outcomes (number of hospitalizations, days in hospital) are also count measures, negative binomial outcomes will be compared with Poisson regression accounting for overdispersion to determine the overall treatment effect. While it is usually customary to match the sample size calculation technique to analysis approach, in this case insufficient published data is available to calculate a sample size for a marginal techniques (Generalized Estimating Equations - GEE) that is proposed as our primary analytic technique. While GEE models represent the main question being studied (the impact of the intervention on population measures of ED use), conditional models can also provide useful information and sample size techniques require fewer assumptions. For this reason, both marginal and conditional (random effects models) will be fit and compared during the data analysis phase of this study. The choice of the most appropriate representation of the overdispersion of data (Negative binomial versus the use of an overdispersion factor in a poisson regression) is highly dependent on the variance structure observed in the collected data (Ver Hoef & Boveng, 2007); hence, the covariance estimates of the observed data will inform final model selection. GEE and mixed effects models will be compared to account for the repeated measurement of participants. A literature review and the presence of clinically significant differences in baseline data will determine which, if any, covariates require adjustment in the final model, and these will be included as covariates in the generalized linear regression models. Other secondary normally distributed outcomes (quality of life, service satisfaction) with be analysed using linear regression using the same principles of adjustment for clinically important covariates, and marginal versus conditional approaches.

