
Given the possibility of missing data in following participants for 12 months who may have unstable housing or community connections, imputation methods will be used to estimate the overall impact of missing data on outcomes. Administrative data from the Institute of Clinical and Evaluative will be used for the purposes of evaluating the primary outcome, and comparing the impact of missing data on outcomes.

*Economic Evaluation Plan*

The objective of the economic evaluation is to compare the cost-effectiveness of the CATCH-ED intervention with usual care, using patient-level data from the randomized clinical trial and linked administrative data at the Institute for Clinical Evaluative Sciences (ICES), Toronto. The Ontario MOHLTC perspective will be used in the analysis. In Ontario, the Ministry pays for physician visits, laboratory tests, imaging, hospitalization, emergency department visits, same day surgery/ procedure, complex continuing care and some home care services. In addition, the Ministry pays for prescription drugs for those older than 65 years old, live in a Long-Term Care Home or a Home for Special Care or enrolled in special programs such as the Ontario Disability Support Plan (ODSP). The time horizon for the economic evaluation will be 12 months (maximum follow-up of the trial).

The primary outcome will be the incremental cost per quality-adjusted life-year (QALY) gained though the intervention compared with usual care. The secondary outcomes include the incremental cost per ED visit avoided and incremental cost per hospital-day avoided.

Measuring QALYs: A QALY is a year of life experienced with a particular health-related quality of life (HRQoL) or health state utility, as represented on a scale from 0 to 1, where 0=death and 1=full health. The EQ-5D and SF-6D (converted from SF-12), generic preference-based instruments that have been used in mental health patients, will be used to assess patients’ health state utility at baseline, 6 months and 1 year. We will calculate each patient’s QALY from the utility scores using the area-under-the-curve approach, with linear interpolation between assessment points (Figure 1).

[figure not shown]

QALY0-90 days

QALY6 -12 months

QALY0-6 months

Figure 1. Calculating QALYs from EQ-5D utility scores

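### Time outside Ontario is asked about for only half of each 6-month primary interval, so temporary absence among participants seen at month 12 can go unrecorded.

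*Protocol*

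**What the plan says.** Protocol, Methods - Outcome Evaluation, gives two lists of interview content. Participants "complete survey interviews at baseline, 6 and 12 months to assess health status, mental health, substance use, self reported acute care service use", together with satisfaction and working alliance. The 3- and 9-month interviews assess service use and also "confirm their contact information and any time spent outside the Province during the previous three-month period". Out-of-Province time appears only in the second list.

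Under Longitudinal Follow-Up, an interview held more than two weeks either side of its due date is treated as missing for that time point.

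Under Other Administrative Data, provincial databases "will be consulted in the case where participants are lost to follow up at 12 months". The stated aim is "in order to ensure that health service utilization is not affected by death or relocation to another province".

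The linked data are held at ICES, where "population based health information is available, at the patient level, for all Ontarians using formal health services" (Administrative Data Linkage). The Analysis Plan says that these data "will be used for the purposes of evaluating the primary outcome" and defines that outcome as the "proportional change in rate of emergency department visits (ED visits) between pre-intervention and 6-month time intervals post-intervention". The Protocol states no rule for how time away or after death enters the denominator of the rate.

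**The concern.** A rate needs both a count and the time over which events could have been counted. The count comes from an Ontario source, so the relevant time is time alive and in Ontario. The Protocol recognises this, since it collects absence time and sets up a check on death and relocation. But the collection it describes leaves gaps. A participant who is away for part of months 3-6 or 9-12 and returns for the 12-month interview is, as written, neither asked about that absence nor included in the database check.

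The programme aims to connect people with local services, so absence could plausibly differ between arms. Unrecorded absence in the control arm would lower its apparent rate and hide benefit. The same absence in the CATCH-ED arm would exaggerate benefit. A person-time rule can be written later, but it cannot use absence data that were never collected.

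**Working it through.** **Coverage of follow-up by the question**

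| Months | Interview at the end | Out-of-Province time named? |
|---|---|---|
| 0-3 | 3-month | yes |
| 3-6 | 6-month | no |
| 6-9 | 9-month | yes |
| 9-12 | 12-month | no |

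This covers 6 of 12 months, and 3 of 6 months in each 6-month interval of the primary outcome. The look-back is fixed at three months and does not run from the last completed interview. If the 3-month interview is missed, coverage of the first interval therefore falls from 3 of 6 months to 0 of 6. The same holds for the 9-month interview and the second interval.

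**Reach of the database check**

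The Sample Size Calculation section plans 83 per arm and expects attrition of up to 30%. At that maximum, 83 × 0.30 = 24.9, so about 25 per arm would be checked. The other 83 × 0.70 = 58.1, about 58 per arm, would not. Someone who dies before month 12 is necessarily among those checked. So are most people who move away for good, because all five interviews are face-to-face. What remains is temporary absence among the roughly 58.

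**Possible effect on the rate ratio**

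The Protocol gives no absence figure, so the shares below are assumptions. Let uT and uC be the mean fractions of follow-up spent outside Ontario and not removed from the denominator, in the CATCH-ED and control arms. If the visit rate while in Ontario is unaffected by absence,

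observed ratio = true ratio × (1 − uT) / (1 − uC).

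| uT | uC | True 1.00 reads | True 0.80 reads |
|---|---|---|---|
| 5% | 5% | 1.00 | 0.80 |
| 5% | 0% | 0.95 | 0.80 × 0.95 = 0.76 |
| 0% | 5% | 1 / 0.95 = 1.05 | 0.80 / 0.95 = 0.84 |
| 10% | 0% | 0.90 | 0.72 |
| 0% | 10% | 1.11 | 0.89 |

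The 0.80 column is the 20% reduction for which the trial is sized.

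**How much absence 5% represents**

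A share of 5% over 12 months arises if 20% of an arm is away for three months (0.20 × 3/12 = 0.05) or 10% for six months (0.10 × 6/12 = 0.05). If absence in the covered quarters is recorded and removed, all of it must fall in the six uncovered months: 0.05 × 12 = 0.6 months per person, or 0.6/6 = 10% of the uncovered time. The 10% rows need twice that, 20% of the uncovered time, and are an outer range.

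**The case against.** The other side has several good arguments, and most limit the point without removing it.

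- **Counting as zero.** A reader might infer that time dead or out of Ontario will be counted as time with no ED visits. The Protocol does not say so. It specifies a rate, collects absence time and states the aim of keeping death and relocation from affecting utilization. A person-time offset is a model detail that may be in the statistical analysis plan, which is not at hand. This stands, and its absence from the Protocol is no finding.
- **Death and permanent relocation.** A reader might also infer that deaths go undetected. They do not, for the reason given in the working, and most permanent moves are caught in the same way. Extending the check to people just interviewed in person at month 12 would find no further deaths, and nothing shows that it would detect temporary travel.
- **The pre-enrolment year.** Absence before enrolment is not asked about either. But the baseline interview precedes randomization, so earlier absence is balanced between arms in expectation. It does not bias the comparison.
- **The lists may not be exhaustive.** Residential status, for instance, is collected according to the Data Collection Plan but is missing from the list for the baseline, 6- and 12-month interviews. The question may therefore be asked in practice at 6 and 12 months. This is fair, and it is why the point is confined to what is written. But the Protocol assigns this item to two named interviews with a fixed look-back, and a form built from that text would have the gap.
- **Other contact and self-report.** Research assistants contact participants monthly and update tracking information, and acute care use is also self-reported. These may show that someone was away. Neither is stated to record days away, and the ICES data are named for the primary outcome.
- **The size is assumed.** This stands. No absence rate is given, and equal absence has no effect on the ratio.

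**Conclusion.** The point holds as a gap in data collection. As written, half of each 6-month primary interval is not covered by the out-of-Province question, and the 12-month check does not reach temporary absence among those interviewed at month 12. It is a modest weakness that is cheap to close, and it does not by itself undermine the primary analysis.

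Its effect depends on absence differing by arm. At an assumed 5% of person-time in one arm and none in the other, a true ratio of 0.80 would read 0.76 or 0.84, so the error can go either way. Equal absence leaves the ratio unchanged. These figures assume that the absence is not removed from the denominator and that the visit rate while in Ontario does not depend on it. A correct person-time rule would remove the bias from recorded absence, but not from absence in the uncovered months.

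**What to change.** Ask the existing out-of-Province question at the 6- and 12-month interviews as well as at 3 and 9 months. Have each interview cover the whole period since the last completed one, so that a missed interview is made up at the next. State in the Protocol, or by reference to the statistical analysis plan if it is already there, that the person-time for the ED visit rate is the known days alive and in Ontario within each interval. The database check can stay as it is.

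The cost is one short question at two interviews already planned, and one line in the analysis text. The downside is some recall error, which grows when the look-back exceeds three months after a missed interview.
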